## 2.3 Rational

Additive or supradadditive activity of an EGFR TK-I with vinorelbine has been demonstrated in-vitro (5). Clinical synergism has also been described between gefitinib and vinorelbine in NSCLC (6). The use of cytotoxics in a metronomic schedule has not been well investigated in the clinical setting despite emerging pre-clinical data. Using an established oral cytotoxic such as oral vinorelbine in a metronomic dose-schedule is attractive due to the oral route of administration. Preclinical studies have shown that by using cytotoxics in a low-dose protracted manner, endothelial cells are preferentially affected via inhibition of proliferation and induction of apoptosis (7). In addition to this anti-angiogenic mechanism, an anti-vasculogenic process may also be involved that acts by reducing circulating endothelial progenitor mobilization and viability (8). Moreover, it has also been shown that tumours that were selected for high levels of acquired resistance to cytotoxics can be induced to respond by using metronomic doses of chemotherapy (9, 10).

Continuous administration of metronomic oral vinorelbine, given three times a week, has been reported as feasible and well tolerated at doses up to 180 mg total dose per week. Early results showed activity against refractory solid tumors such as renal cancer, NSCLC, ovarian cancer, prostate cancer, unknown primary and Kaposi sarcoma (Briasoulis et al EORTC-NCI-AACR 2006). Eighty patients (39 female and 41 male, median age 58, median PS 1) were treated in this study with a variety of progressive refractory solid cancers and were treated at the dose range of 20 mg (16 pts), 30 mg (17 pts), 40 mg (26 pts), 50 mg (13 pts), 60 mg (6 pts) and 70 mg (2 pts) TTW. Dose limiting toxicity occurred in 2 patients at the 60 mg dose level (leucopenia grade 4 on the 14th week of treatment and epistaxis on the 9th week treatment). Median duration of treatment was 19 weeks (range 4 to 85+ weeks) and corresponded to time to progression, since no withdrawals from therapy were due to toxicity. Objective tumor response was documented in 8 among 52 patients in renal cancer, NSCLC, ovarian cancer, prostate cancer, unknown primary and Kaposi sarcoma while 32% of treated patients had disease control for at least 6 months. A similar metronomic dosing schedule was also shown to be safe and feasible up to 50 mg three times a week (11).

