|                                                                                                     | 30                                                                  | 80                                                   | Level -1   |
|                                                                                                     | 40                                                                  | 100                                                  | Level 1    |
|                                                                                                     | 50                                                                  | 120                                                  | Level 2    |
|                                                                                                     | 60                                                                  | 140                                                  | Level 3    |
|                                                                                                     | 70                                                                  | 160                                                  | Level 4    |
|                                                                                                     | 80                                                                  | 180                                                  | Level 5    |
| Erlotinib
150 mg
(only in the
absence of DLT at
dose level 5 of
vinorelbine) | No DLT at dose level
5 of vinorelbine
(80 mg/m  ) | No DLT at dose level
5 of vinorelbine
(180 mg) |            |

Escalation of Erlotinib dose to 150 mg OM will only start if level 5 oral vinorelbine is reached without dose-limiting toxicities with Erlotinib 100 mg OM in each schedule.

The optimal anti-angiogenic dose of oral vinorelbine given in metronomic schedule will be determined from the Circulating Endothelial Cells/Circulating Endothelial Progenitors (CEC/CEP) assays correlations.

Efficacy will be assessed every 2 cycles during maintenance treatment. Each cycle will last 21 days with a window period of 7 days. Patients on the conventional schedule of vinorelbine who respond or have stable disease, vinorelbine will be stopped after 6 cycles and erlotinib continued. Patients on the metronomic schedule of vinorelbine who respond will continue on both vinorelbine and erlotinib.

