Reported adverse events and potential risks for Oral Vinorelbine and Erlotinib are described in Section 5.2. Appropriate dose modifications for Oral Vinorelbine and Erlotinib are described in Section 6. No investigational or commercial agents or therapies other than those described below may be administered with the intent to treat the patient's malignancy.

| REGIMEN DESCRIPTION |                                                                                                                                                                                                  |                                             |              |                                                                                                                                      |                     |
|----------------------------|--------------------------------------------------------------------------------------------------------------------------------------------------------------------------------------------------|---------------------------------------------|--------------|--------------------------------------------------------------------------------------------------------------------------------------|---------------------|
| Agent               | Premedications; Precautions                                                                                                                                                               | Dose                                 | Route | Schedule                                                                                                                      | Cycle Length |
| Vinorelbine                | Both erlotinib and vinorelbine will be given after prophylactic administration of antiemetics (preferably 5-HT 3 antagonist) on Day 1 (except for Cycle 1) and on Day 8 of each cycle | Dose as appropriate for assigned dose level | Oral         | Conventional Schedule: Day 1 and 8 of each cycle
Metronomic Schedule: D1,3,5 every 7 days for 3 weeks of each cycle | 21 days (3 wks)     |

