#### 5.1.1 Oral vinorelbine

Oral ondansetron may be used as prophylactic anti-emetic before administration of vinorelbine on CSV. Full blood counts will be required on Days 1,8,15 of cycle 1 and days 1 and 8 of each subsequent cycle prior to vinorelbine dosing for patients on CSV, and days 1,8, 15 of cycle 1 and day 1 only of every subsequent cycle on MSV. On CSV, for patients who have respond or stable at disease, vinorelbine will be discontinued after 6 cycles. Full blood count is not required for day 8 of cycle 7 and subsequent cycles.

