## 6. DOSING DELAYS/DOSE MODIFICATIONS

If patient should encounter significant toxicity in the first cycle of treatment, treatment will be delayed until the recovery of the toxicity. Any delay beyond 2 weeks will result in removal from trial. The subsequent cycle will be started at the next lower dose level (see table).

In addition, the occurrence of a clinically significant toxicity that deemed related to either vinorelbine or erlotinib, in view of safety of the patient, that study drug can be discontinued. Patient will be allowed to continue in the trial with single agent therapy.

| Dose Level | Vinorelbine Dose
(Conventional Schedule) | Vinorelbine Dose (Metronomic
Schedule) |
|-------------------|-----------------------------------------------------|---------------------------------------------------|
| -1                | 30 mg/m^2, D1,D8 schedule          | 80 mg/week, D1,3,5 every 7 days            |
| 1                 | 40 mg/m^2, D1,D8 schedule          | 100 mg/week, D1,3,5 every 7 days           |
| 2                 | 50 mg/m^2, D1,D8 schedule          | 120 mg/week, D1,3,5 every 7 days           |
| 3                 | 60 mg/m^2, D1,D8 schedule          | 140 mg/week, D1,3,5 every 7 days           |
| 4                 | 70 mg/m^2, D1,D8 schedule          | 160 mg/week, D1,3,5 every 7 days           |
| 5                 | 80 mg/m^2, D1,D8 schedule          | 180 mg/week, D1,3,5 every 7 days           |
| Dose Level | Erlotinib Dose                               | Erlotinib Dose                             |
| 1                 | 100 mg, daily schedule                       | 100 mg, daily schedule                     |
| 2                 | 150 mg, daily schedule                       | 150 mg, daily schedule                     |

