| Other tests, as appropriate                                                                                                                                                                                                                                                                                                                                                                                                                                           |                 |                                                                                                                                                                                                                                       |   |   |   |   |   |   |   |   |   |                |  |                |
| Pharmacokinetic studies                                                                                                                                                                                                                                                                                                                                                                                                                                               | See section 9.0 |                                                                                                                                                                                                                                       |   |   |   |   |   |   |   |   |   |                |  |                |
| a: vinorelbine and erlotinib: Dose as assigned; oral.
b: Albumin, alkaline phosphatase, total bilirubin, bicarbonate, BUN, chloride, creatinine, glucose, LDH, potassium, total protein, SGOT[AST], SGPT[ALT], sodium.
c: Serum pregnancy test (women of childbearing potential).
d: Off-study evaluation.
e: For subjects who respond or stable at disease , cycle duration will extend from 3 weekly to 6 weekly after 6 months (8cycles) of treatment. |                 |                                                                                                                                                                                                                                       |   |   |   |   |   |   |   |   |   |                |  |                |

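### Calendar footnote e lengthens the cycle to 6 weeks for all responding or stable patients, so for those still on metronomic vinorelbine the late blood-count interval either doubles or contradicts Section 5.1.1

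*Protocol*

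**What the plan says.** Three parts of the protocol bear on this.

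- **Cycle length.** Section 5.1 states: "Each cycle will last 21 days with a window period of 7 days". Section 9.1.1 also defines one treatment cycle as three weeks for both schedules. Neither section mentions a later change. Section 10, footnote e, says that for patients who respond or are stable, "cycle duration will extend from 3 weekly to 6 weekly after 6 months (8cycles) of treatment". In the calendar, mark e sits on the beyond-week-25 cells for physical examination, vital signs, weight, performance status, blood count and serum chemistry.
- **Who is still on vinorelbine.** Under Section 5.1, conventional-schedule (CSV) patients who respond or are stable stop vinorelbine after 6 cycles and keep erlotinib. For the other schedule it says: "Patients on the metronomic schedule of vinorelbine who respond will continue on both vinorelbine and erlotinib". No cycle cap is given, and Section 5.4 lets treatment run indefinitely. MSV dosing in Section 6 is weekly without weeks off, for example "180 mg/week, D1,3,5 every 7 days" at level 5.
- **Blood counts.** After cycle 1, Section 5.1.1 asks for counts on "day 1 only of every subsequent cycle on MSV". It thins the CSV counts only once CSV vinorelbine has stopped: "Full blood count is not required for day 8 of cycle 7 and subsequent cycles".

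**The concern.** MSV counts are scheduled per cycle, so changing the length of a cycle changes the count interval. Footnote e makes that change at a point where CSV responding or stable patients have already stopped vinorelbine but MSV responders have not. One rule therefore covers two groups with different needs, and the protocol gives no reason for relaxing counts in patients who are still on a myelosuppressive drug.

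What is at stake is late safety monitoring. Section 2.1.1 names neutropenia as the dose-limiting toxicity of vinorelbine, advises a count before each dose, and advises against dosing below 1500 neutrophils/mm³. MSV already departs from that advice, with one count per 21 days after cycle 1. Footnote e may widen the gap again, and two sites could follow different intervals while each cites the protocol.

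**Working it through.** **The plan's own figure.** 8 cycles × 21 days = 168 days = 24 weeks, about 5.5 months, which the footnote rounds to 6. Day 1 of cycle 9 falls in week 1 + 8 × 3 = 25, matching the last treatment column of the calendar. So the footnote takes effect from week 25.

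**Inputs.**
- MSV dosing: 3 doses per week (Section 5.1 regimen table; Section 6).
- Scheduled MSV counts after cycle 1: one per cycle (Section 5.1.1).
- Cycle length: 3 weeks (Sections 5.1 and 9.1.1) or 6 weeks (footnote e).

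**Formulas.** Doses in 24 weeks = 3 × 24 = 72. Counts in 24 weeks = 24 ÷ interval in weeks. Doses per count = 72 ÷ counts.

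| Next 24 weeks, MSV patient on continuous dosing | Interval | Counts | Doses per count |
|---|---|---|---|
| 21-day cycle, Section 5.1.1 | 3 weeks | 24 ÷ 3 = 8 | 72 ÷ 8 = 9 |
| 6-week cycle, footnote e | 6 weeks | 24 ÷ 6 = 4 | 72 ÷ 4 = 18 |

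At level 5, the vinorelbine taken between scheduled counts is 180 × 3 = 540 mg on the 3-week interval and 180 × 6 = 1080 mg on the 6-week interval. At level 1 it is 300 mg and 600 mg.

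**The two ways to read the text.**
1. The treatment cycle really becomes 42 days. Section 5.1.1 and the calendar cell then agree on one count per 6 weeks. But Sections 5.1 and 9.1.1 are contradicted, and the count interval for patients on continuous vinorelbine has doubled without comment.
2. Only the marked calendar rows move and the treatment cycle stays at 21 days. Section 5.1.1 then requires 8 counts per 24 weeks while the calendar cell gives 4.

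The protocol does not say which applies.

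**CSV for comparison.** Responding or stable CSV patients stop vinorelbine after 6 × 3 = 18 weeks, before week 25. A 6-weekly count raises no such question for them.

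**The case against.** The strongest reply is that the 6-week interval is deliberate and coherent. Section 5.1 assesses efficacy every 2 cycles, and Section 11 moves imaging to every 12 weeks after 6 months. The two agree at that stage only if the late cycle is 6 weeks (2 × 6 = 12). Footnote e would then be the specific late rule, Section 5.1 the general one, and what remains would be a judgement about how often to count. This has force: a longer late interval was probably intended. It does not show that a 6-weekly count was intended for patients still taking vinorelbine. Section 5.1.1 relaxes CSV counts only after the drug stops, and footnote e makes no such distinction for MSV.

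The safety evidence is also thin. Section 2.1.1 calls the neutropenia rapidly reversible and non-cumulative. In the metronomic study described in Section 2.3, the two dose-limiting events came in weeks 9 and 14 at 60 mg three times a week (180 mg/week, MSV level 5), when counts here would still be 3-weekly. Median treatment there was 19 weeks, short of week 25, and no withdrawal was due to toxicity. Adverse event evaluation continues, and the calendar allows other tests as appropriate. All of this stands. The week-14 leucopenia shows that onset after cycle 1 is possible; it is not evidence of risk beyond week 24.

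A reader might infer something stronger: since the regimen table gives MSV dosing as "D1,3,5 every 7 days for 3 weeks of each cycle", a 6-week cycle would insert a 3-week break and halve the dose. The documents do not support this. That table row states a cycle length of 21 days, so its three weeks are the whole cycle. Section 6 gives weekly doses with no weeks off, and Section 2.3 builds on "Continuous administration of metronomic oral vinorelbine, given three times a week". No section describes a break, and as far as the calendar can be read, the drug rows carry no mark e.

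**Conclusion.** The inconsistency is real and minor. Footnote e conflicts with the 21-day cycle in Sections 5.1 and 9.1.1. For MSV patients on continuous vinorelbine, it either doubles the scheduled count interval from 21 to 42 days (18 instead of 9 doses per count) or contradicts Section 5.1.1 (6-weekly against 3-weekly).

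This rests on MSV dosing continuing three times a week beyond week 24, which is the natural reading. The number of patients affected is not given and is probably small. Section 5.1 names only MSV responders as continuing both drugs; stable MSV patients come in through the general duration rule in Section 5.4.

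A reader might also infer that dose finding is compromised. It is not: Section 5.2 ties the haematological and non-haematological dose-limiting toxicities to the first cycle. Only the 14-day-delay criterion has no stated cycle limit, so the maximum tolerated dose is essentially unaffected.

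**What to change.** - Reword footnote e so that only the clinic visit interval extends to 6 weeks after 8 cycles. State that the treatment cycle stays at 21 days and that MSV vinorelbine continues on days 1, 3 and 5 of every week.
- State on the blood-count row and in Section 5.1.1 that any patient still taking vinorelbine has a count every 3 weeks, including beyond week 25, and that the 6-weekly count applies only to patients off vinorelbine.
- As a consequence, give the late efficacy interval in Section 5.1 in weeks. With a 21-day cycle, every 2 cycles means 6 weeks, not the 12 weeks in Section 11.

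The cost is wording in these places, plus 8 − 4 = 4 extra routine blood counts per 24 weeks for each affected MSV patient. These can be taken without a full clinic visit. The sponsor should confirm that uninterrupted MSV dosing is what was meant.

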## 11. MEASUREMENT OF EFFECT

Although response is not the primary endpoint of this trial, patients with measurable disease will be assessed by standard criteria. For the purposes of this study, patients should be re-evaluated every 6 weeks for the first 6 months and subsequently every 12 weeks unless disease progression. In addition to a baseline scan, confirmatory scans will also be obtained 6 weeks following initial documentation of an objective response.

For patients who are discontinued from the study for reasons other than disease progression, tumor evaluation by RECIST will not be necessary once new anti-neoplastic cancer therapy has begun.

### 11.1 Antitumor Effect – Solid Tumors

Response and progression will be evaluated in this study using the new international criteria proposed by the Response Evaluation Criteria in Solid Tumors (RECIST) Committee [JNCI 92(3):205-216, 2000]. Changes in only the largest diameter (unidimensional measurement) of the tumor lesions are used in the RECIST criteria.

#### 11.1.1 Definitions

Evaluable for toxicity. All patients will be evaluable for toxicity from the time of their first treatment with Vinorelbine.

Evaluable for objective response. Only those patients who have measurable

disease present at baseline, have received at least one cycle of therapy, and have had their disease re-evaluated will be considered evaluable for response. These patients will have their response classified according to the definitions stated below. (Note: Patients who exhibit objective disease progression prior to the end of cycle 1 will also be considered evaluable.)

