### 3. PATIENT SELECTION

#### 3.1 Eligibility Criteria

3.1.1 Patients must have histologically or cytologically confirmed *NSCLC*

3.1.2 *At least one or two prior lines of chemotherapy for metastatic disease or locally advanced unresectable disease.* There should be at least 4 weeks since prior chemotherapy or radiation therapy or 6 weeks if the last regimen included BCNU or mitomycin C

3.1.3 Age  $\geq$  21 years.

3.1.4 ECOG performance status  $<2$  (Karnofsky  $>60\%$ , see Appendix A).

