## 3.2 Exclusion Criteria

- 3.2.1 Patients who have had chemotherapy or radiotherapy within 4 weeks (6 weeks for nitrosoureas or mitomycin C) prior to entering the study or those who have not recovered from adverse events due to agents administered more than 4 weeks earlier.
- 3.2.2 Patients may not be receiving any other investigational agents.
- 3.2.3 Patients who have received previous vinorelbine or oral EGFR tyrosine kinase inhibitors
- 3.2.4 Patients with *progressive* brain metastases should be excluded from this clinical trial because of their poor prognosis and because they often develop progressive neurologic dysfunction that would confound the evaluation of neurologic and other adverse events. *However patients are eligible if they have brain metastases that have been treated with whole brain radiotherapy and are stable and not on corticosteroids.*
- 3.2.5 History of allergic reactions attributed to compounds of similar chemical or biologic composition to Oral Vinorelbine or other agents used in study.
- 3.2.6 Prior and / or concomitant treatment with drugs known to induce or inhibit cytochrome P450 3A4, CYP1A1 & CYP1A2 : phenytoin, carbamazepine, barbiturates, rifampicine, imidazole antifungals (such as ketoconazole, fluconazole, itraconazole, metronidazole), omeprazole and ritonavir *within 1 week of starting protocol treatment.*
- 3.2.7 Significant malabsorption syndrome or disease affecting the gastro-intestinal tract function
- 3.2.8 Uncontrolled intercurrent illness including, but not limited to, ongoing or active infection, symptomatic congestive heart failure, unstable angina pectoris, cardiac arrhythmia, or psychiatric illness/social situations that would limit compliance with study requirements.
- 3.2.9 Pregnancy or breast feeding or women of child-bearing potential not using effective contraception.

3.2.10 HIV-positive patients on combination antiretroviral therapy are ineligible because of the potential for pharmacokinetic interactions with Oral Vinorelbine. In addition, these patients are at increased risk of lethal infections when treated with marrow-suppressive therapy. Appropriate studies will be undertaken in patients receiving combination antiretroviral therapy when indicated.

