#### 11.1.2 Disease Parameters

Measurable disease. Measurable lesions are defined as those that can be accurately measured in at least one dimension (longest diameter to be recorded) as  $\geq 20$  mm with conventional techniques (CT, MRI, x-ray) or as  $\geq 10$  mm with spiral CT scan. All tumor measurements must be recorded in millimeters (or decimal fractions of centimeters).

Non-measurable disease. All other lesions (or sites of disease), including small lesions (longest diameter  $< 20$  mm with conventional techniques or  $< 10$  mm using spiral CT scan), are considered non-measurable disease. Bone lesions, leptomeningeal disease, ascites, pleural/pericardial effusions, lymphangitis cutis/pulmonis, inflammatory breast disease, abdominal masses (not followed by CT or MRI), and cystic lesions are all non-measurable.

Target lesions. All measurable lesions up to a maximum of 5 lesions per organ and 10 lesions in total, representative of all involved organs, should be identified as **target lesions** and recorded and measured at baseline. Target lesions should be selected on the basis of their size (lesions with the longest diameter) and their suitability for accurate repeated measurements (either by imaging techniques or clinically). A sum of the longest diameter (LD) for all target lesions will be calculated and reported as the baseline sum LD. The baseline sum LD will be used as reference by which to characterize the objective tumor response.

Non-target lesions. All other lesions (or sites of disease) including any measurable lesions over and above the 10 target lesions should be identified as **non-target lesions** and should also be recorded at baseline. Measurements of these lesions are not required, but the presence or absence of each should be noted throughout follow-up.

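### Section 11.1.2 lets previously irradiated lesions into the target-lesion sum, which can distort the PR/SD split and can score PD as SD in the clinical benefit rate

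*Protocol*

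**What the plan says.** **Who is evaluable.** Protocol Section 11.1.1 limits response evaluation to patients with measurable lesions: "disease present at baseline, have received at least one cycle of therapy, and have had their disease re-evaluated will be considered evaluable for response".

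**What is measurable.** Section 11.1.2 states: "Measurable lesions are defined as those that can be accurately measured in at least one dimension". The thresholds are 20 mm by conventional techniques and 10 mm by spiral CT. The kinds of lesion it names as non-measurable are "Bone lesions, leptomeningeal disease, ascites, pleural/pericardial effusions, lymphangitis cutis/pulmonis, inflammatory breast disease, abdominal masses (not followed by CT or MRI), and cystic lesions". Irradiated lesions and parenchymal brain metastases are not among them.

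**What is a target lesion.** The same section takes as targets "All measurable lesions up to a maximum of 5 lesions per organ and 10 lesions in total, representative of all involved organs". Selection goes by size and by suitability for repeated measurement. The only measurable lesions it assigns to the non-target group are those above the cap.

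**Who can enter.** Section 3.1.2 says: "There should be at least 4 weeks since prior chemotherapy or radiation therapy". Section 3.2.1 excludes "Patients who have had chemotherapy or radiotherapy within 4 weeks". Neither restricts the irradiated site or asks for progression there since radiotherapy. Section 3.2.4 adds that "patients are eligible if they have brain metastases that have been treated with whole brain radiotherapy and are stable and not on corticosteroids".

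**The concern.** Read together, these sections let a lesion that was recently irradiated, or that was accepted because it is stable after irradiation, contribute to the sum that decides CR, PR, SD and PD. Its behaviour may reflect the radiotherapy and not the study drugs. A patient whose only measurable lesion was irradiated is also evaluable for response.

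The endpoints at stake are the response categories, which Section 13.1 summarises by dose, and the clinical benefit rate (CR+PR+SD), a secondary endpoint in Sections 1.2 and 11.1.4.3. Two separate errors are possible: shrinkage credited to the drugs, and growth elsewhere diluted by a lesion that does not change. They affect the endpoints differently and need separate checks.

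**Working it through.** The protocol gives no figure to reproduce. The check uses its own windows and thresholds. Lesion sizes and shares are assumed for illustration.

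**Inputs**
- Radiotherapy at least 4 weeks (28 days) earlier: Sections 3.1.2 and 3.2.1.
- Baseline scan up to 4 weeks (28 days) before treatment: Section 11.1.3.
- First re-evaluation at 6 weeks (42 days): Section 11.
- PR: sum down at least 30% from baseline. PD: sum up at least 20% from the smallest sum since treatment started, or a new lesion: Section 11.1.4.1.
- SD: documented once, at least 4 weeks from baseline: Section 11.1.4.3.

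**1. Timing.** Assume that entry is the start of treatment. The shortest gap from the end of radiotherapy to the baseline scan is 28 − 28 = 0 days. The first re-evaluation then falls 28 + 42 = 70 days after radiotherapy. Radiotherapy shrinkage can therefore lie between the two scans.

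**2. Shrinkage scored as PR.** Let irradiated lesions be a share s of the baseline sum and shrink by a fraction x, with the rest unchanged. PR needs s·x ≥ 0.30, so x ≥ 0.30/s.
- s = 0.25: 1.20, impossible
- s = 0.50: 0.60
- s = 0.75: 0.40

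Example: irradiated 40 → 15 mm and unirradiated 30 → 34 mm. The sum goes 70 → 49 mm, and −21/70 = −30.0%, so PR. The unirradiated lesion alone is +4/30 = +13.3%, so SD. The patient counts in CR+PR+SD either way. The PR/SD split changes and the clinical benefit rate does not.

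**3. Static lesion hiding PD.** Let the irradiated share s stay constant and the other target lesions grow by g, with the baseline sum as the smallest sum. PD needs (1 − s)·g ≥ 0.20, so g ≥ 0.20/(1 − s).

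| s | growth needed elsewhere |
|---|---|
| 0 | 20% |
| 0.25 | 26.7% |
| 0.40 | 33.3% |
| 0.50 | 40% |
| 0.75 | 80% |

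Example: irradiated brain lesion 30 → 30 mm and lung lesion 20 → 25 mm. The sum goes 50 → 55 mm, +10%, so SD. The lung lesion alone is +5/20 = +25%, so PD. This patient is moved into the clinical benefit rate.

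**4. Effect of the nadir reference.** Irradiated 50 → 30 mm and untreated 50 → 70 mm leave the sum at 100 mm, so SD, although the untreated lesion grew 40%. If an intermediate scan catches the shrinkage first (30 + 50 = 80 mm), the later 100 mm is +20/80 = +25%, so PD. The nadir rule therefore limits masking by a shrinking lesion. It gives no such protection in step 3, where the smallest sum is the baseline sum.

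**The case against.** - **The protocol nowhere says that irradiated lesions count.** It cites the published RECIST criteria as its method and asks for lesions suited to accurate repeated measurement. Both facts are true. However, Section 11.1.1 classifies response by the definitions written out below it, and those have no condition on irradiation. Suitability for measurement is a different matter from prior treatment. Whether the cited criteria restrict irradiated lesions cannot be checked from the protocol.
- **False PR does not inflate the clinical benefit rate.** This stands. A reader might infer that every radiotherapy response adds to the rate. With the other lesions stable, the patient is SD without the irradiated lesion and is counted anyway. Only PD scored as SD raises the rate.
- **Other rules catch progression.** This stands in part. New lesions and unequivocal non-target progression give PD whatever the sum, and the nadir reference works as in step 4. Growth confined to target lesions beside a static irradiated lesion is still diluted.
- **Brain metastases are an unlikely source of shrinkage.** This stands. They must be stable to be admitted, and must also meet the size threshold. They fit the static mechanism better. Bone and leptomeningeal lesions are already non-measurable.
- **Confirmation protects PR.** Only partly. Section 11 asks for a confirmatory scan 6 weeks after a response, but shrinkage that persists would pass it.

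**Conclusion.** The gap is real and modest. Followed as written, Sections 11.1.1 and 11.1.2 with the eligibility rules allow irradiated lesions into the target sum. Radiotherapy shrinkage can be reported as PR, which mainly distorts the PR/SD split. A static irradiated share raises the PD threshold for the remaining target lesions to 27% at s = 0.25 and 40% at s = 0.50, and this can inflate the clinical benefit rate. A static share also makes PR harder to reach, so the bias in PR alone can go either way.

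Two stronger readings are not supported. One patient moves the rate by 1/6 = 16.7 points in a cohort of 6 or 1/3 = 33.3 points in a cohort of 3, and a reader might take that as the size of the bias. It is only the step that any single patient makes. The protocol does not give the share of affected patients, so no expected bias can be stated. A reader might also infer that dose finding is compromised. DLT and MTD do not use tumour response, and the response endpoints are descriptive, with no test or threshold attached.

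The arithmetic rests on assumed lesion sizes and shares. The 0-day and 70-day gaps also assume that entry coincides with the start of treatment.

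**What to change.** **Section 11.1.2.** State that a lesion in a previously irradiated field, including treated brain metastases, is recorded as non-target unless progression in that lesion since radiotherapy is documented.

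**Section 11.1.1.** Require, for response evaluability, at least one measurable lesion that lies outside such a field or has progressed since the radiotherapy.

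**Patients with only irradiated, non-progressed lesions.** Treat them as not evaluable for response and list them separately. They should not be brought into the clinical benefit rate through the non-target criteria. Section 11.1.1 limits response evaluation to measurable disease, and Section 11.1.4.2 would score a persisting irradiated lesion as stable disease, which restores the upward bias.

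**Cost.** Short additions to Section 11, with no extra scans or patients. A few patients will have fewer target lesions or leave the response-evaluable set. The wording should be settled before response data are read.
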